	**Pearson correlation coefficient**		
	0.10	0.15	0.20
**Sample size**		**Power**	
500* (450)	0.35	0.76	0.96
750* (675)	0.54	0.92	> 0.99
1000* (900)	0.69	0.98	> 0.99

*Adjusted sample size accounting for 10% attrition

### Statistical analysis

The major analyses will be estimation of correlation coefficients between continuous variables, such as the correlations between maternal glycemia and offspring body size. To examine the roles of potential mediators on the relationship between maternal BMI, weight gain and glycemia with offspring body size, adiposity and metabolic outcomes, a series of linear regression models will be used in accordance with the coefficients mediation method described by MacKinnon et al. [20]. Analyses of the effect of maternal epigenetic or transcriptional changes in the serial samples will be performed using similar methods. Additional methods may also be used because statistical methods for mediation analysis are evolving.

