**Methods:**

ETCHED is a longitudinal observational study of American Indian/Alaska Native (AI/AN) and Hispanic pregnant woman and their offspring. Pregnant mothers ≥ 18 years old are enrolled at a large public hospital system in the southwestern US. Enrolled mothers are followed through pregnancy, delivery, and the maternal/offspring dyad will be followed until the child’s 18th birthday. At each maternal visit, questionnaires assessing medical history, diet, physical activity, sleep, perceived stress, and socioeconomic and sociocultural information are obtained. Standard laboratory tests during maternal visits include glycemic measures, lipids, and renal function. Additional bio samples obtained include venous blood samples and cord blood for obesity/metabolic biomarkers and genetic/epigenetic testing, urinalysis, placental tissue for examining functional pathways, breast milk for metabolomics, and stool for metabolites and microbiome analysis. The offspring will have 6 infant/toddler visits at 6–12 weeks, 4 months, 6 months, 18 months, 2 and 3 years respectively. Thereafter, they will undergo comprehensive research visits (major visits) at 4–5 years, 6–9 years, 10–13 years, and 14–17 years. The major visits in children include detailed medical history, anthropometry, developmental assessment, socioeconomic and environmental assessments (food insecurity, family structure, and childcare), feeding and activity, biochemical tests, genetics/epigenetic testing, and ultrasound elastography. Electronic health records will be reviewed for additional clinical information. The primary analysis will constitute estimation of correlation coefficients between continuous variables. The planned study duration in this ongoing study is 23-years.

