### Study outcomes and data collection

The primary outcomes are birth weight, and weight, length, and age/sex adjusted BMI percentile and z-scores at 6–12 weeks, 4, 6, 12, 18, and 24-months. Secondary outcomes include BMI percentile and z-scores from 2 to 18 years of age, stool microbiome (microbial taxonomies, microbial pathways), hepatic steatosis and fibrosis, neurocognitive development, assessments of environmental and psychosocial status and biochemical measures for glycemia, lipids, renal, and liver function.

Data are collected either by in-person assessment, by review of medical records, by phone or other virtual media or a combination following the schedule of activities in Table 1. Data collected on mothers include demographics, anthropometric measures, socioeconomic and family environment history, medical history, obstetric history, laboratory evaluations, and biospecimens (blood, urine, stool, cord blood, placental tissue, and breast milk). Data collected on offspring include demographics, birth history, socioeconomic history such as living situation, childcare arrangements, parental education and employment, food insecurity, cultural practices during pregnancy, medical history, assessments of lifestyle habits such as eating and activity patterns, sleep, perceived stress, laboratory evaluations, and biospecimens (blood, urine, and stool). DNA and RNA data are collected on both mothers and offspring. The data collected in ETCHED are summarized in Table 2. Some of the information related to medical history of mothers and/or offspring is obtained by direct interview, by review of medical records, or both.

**Table 2 Tab2:** Data collected in ETCHED

Participant	Type	Collected data
Mother	Demographic, socioeconomic and family environment history	• Age, race/ethnicity, marital status, approximate age of child’s father, father’s race ethnicity, father’s diabetes status • Highest level of education of parents, family size, family employment history, family income, family ownership, family hardships, household characteristics • Childcare arrangements
	Medical record review	• Clinical information, laboratory and radiological information • This includes demographic, anthropometric, clinical history, results of imaging studies, and biochemical data (will focus on periodic measures related to glycemia).
	Medical history	• Underlying health conditions, new illnesses or hospitalizations between visits, maternal history of COVID-19 infection

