	Obstetric history	• Pre-pregnancy weight, delivery date(s), APGAR score, sex, weight, length, gestational age, prenatal and perinatal history, pregnancy outcomes
	Laboratory evaluations	• From blood: blood complete blood count, HbA1c, fasting glucose and insulin, adiponectin, TNF, IL-6, folate, CRP, and cytokines, biological markers for obesity and metabolic dysfunction, liver function tests, serum cholesterol, triglycerides, HDL and LDL cholesterol, apolipoproteins • Oral glucose tolerance test in the research clinic postpartum
	Biospecimens	• Blood for DNA, RNA • Stool for microbiome analysis • Breastmilk
	Mother’s procedures	• Physical exam [height, weight, waist circumference (non-pregnant) and blood pressure measurement] • Questionnaires: Unmet Social Support, Modifiable Activity Questionnaire, Pittsburg Sleep Quality Index, Adverse Childhood Experience, BLOCK-2000, Food Insecurity Questionnaire, Eating Behaviors (EARLY), Cohen’s perceived Stress Scale, Short Acculturation Scale for Hispanics (SASH) if appropriate, and cultural consideration survey
Infant	Birth history (by medical record review)	• Neonatal history such as mode of delivery, birth, weight, height, and head circumference, gestational age, APGARS, neonatal/perinatal complications, congenital anomalies
	Medical history	• Mother will be asked about: vaccination history, history of illness, including COVID diagnosis, antibiotics use, hospitalizations, ED visits, any new diagnosis.
	Medical record review	• Clinical, laboratory, and radiological information
	Laboratory evaluation	• Blood will be drawn for CBC, HbA1c, insulin, and lipids
	Biospecimens	• Cord blood for Hba1c, insulin, biomarkers such as c-peptide, leptin, adiponectin, TNF-alpha; other novel metabolomics, genetic and epigenetic tests. SARS-COVID 19 antibody • Placenta tissue for subsequent analysis of placenta function, methylome, transcriptome, proteome, metabolome, histopathology and histochemistry • Blood draw for DNA and RNA • Meconium and stool for microbiome analysis

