### Sample size and power calculation

Table 3 shows the power to detect correlations of at least a given magnitude at *p* < 0.01 for recruited sample sizes of 500, 750, or 1000 paired observations (mother-child pairs, calculated with adjustment assuming 10% attrition). An alpha level of 0.01 was selected because four primary analyses are planned to correlate maternal glycemia, serum lipids, inflammatory markers, and kidney function with each primary outcome (offspring birthweight and body size up to 24 months of age). A target sample size of 750 maternal-offspring pairs is proposed, as this will provide ~ 90% power to detect a correlation coefficient of 0.15, which we take to be biologically meaningful (Table 3). Genome-wide genetic and epigenetic studies (and other studies in which large numbers of exposure variables are measured simultaneously) will require more stringent control of type I error to account for multiple testing; typically, this requires *P* < 10^− 7^ [18]. With such stringency, effect sizes will need to be somewhat larger than in standard analyses for reliable detection; with the target sample size of 750, the minimum detectable correlation at *P* < 10^− 7^ with 80% power is 0.23. We will use the false discovery rate procedure to control the type I error rate [19].

**Table 3 Tab3:** Sample size and power calculations

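### The primary analysis is stated as correlation coefficients with no adjustment named, so it cannot separate three related maternal exposures and leaves age and sex variation in birth weight, infant weight and length

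*Protocol article*

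**What the plan says.** The abstract states: "The primary analysis will constitute estimation of correlation coefficients between continuous variables". The Statistical analysis section repeats it: "The major analyses will be estimation of correlation coefficients between continuous variables, such as the correlations between maternal glycemia and offspring body size". The study is sized on the same quantity. Table 3 is headed "Pearson correlation coefficient", and the text claims "power to detect a correlation coefficient of 0.15, which we take to be biologically meaningful".

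Elsewhere, linear regression is introduced only to examine mediators. The section on the primary outcomes adds scatterplots, box plots and a growth-curve model of BMI in which time is the only predictor named.

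The primary objective names three exposures: pre-pregnancy BMI, gestational weight gain and glycemia. The outcomes are given as "The primary outcomes are birth weight, and weight, length, and age/sex adjusted BMI percentile and z-scores at" six postnatal time points, the first being 6–12 weeks. The age/sex wording attaches to BMI, not to birth weight, weight or length.

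The obstetric history in Table 2 shows that the obvious covariates are collected: "Pre-pregnancy weight, delivery date(s), APGAR score, sex, weight, length, gestational age, prenatal and perinatal history, pregnancy outcomes". Maternal age and race/ethnicity are in the same table.

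**The concern.** Three consequences follow if the analysis is run as stated.

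- **Related exposures.** Pre-pregnancy BMI, weight gain and glycemia plausibly move together. One correlation per exposure cannot show which of them carries the association with offspring size.
- **Age and sex variation left in the outcome.** Raw weight at a visit spread over six weeks of rapid growth varies with the day of measurement. That variation is noise for the maternal association, and it lowers both the correlation and the power.
- **A built-in correlation.** If gestational weight gain means total gain, it contains the fetus and rises with length of gestation, as birth weight does. Part of that correlation would exist without any effect of maternal gain.

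At stake are the interpretation of the primary result and, for the 6–12 week weight, the power that the sample size was chosen to deliver.

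**Working it through.** **Inputs from the protocol article.** 750 pairs recruited, 675 after 10% attrition; alpha 0.01; target r = 0.15. Sidedness is not stated, so two-sided is assumed.

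**1. The plan's own figure.** Fisher z: power = Φ(atanh(r)·√(n−3) − 2.576). For r = 0.15 and n = 675: 0.1511 × √672 = 3.918; 3.918 − 2.576 = 1.342; power 0.910. The text says about 90% and Table 3 says 0.92, so the figure is reproduced to within about one point. The smallest significant correlation is tanh(2.576/√672) = 0.099.

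**2. Related exposures.** If exposure X has no association with outcome Y once a shared factor C is held fixed, the raw correlation is r(XC) × r(YC). The article gives neither value, so both are assumptions:

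| r(XC) × r(YC) | raw r | chance of p < 0.01, n = 675 |
|---|---|---|
| 0.2 × 0.2 | 0.04 | 0.06 |
| 0.2 × 0.4 | 0.08 | 0.31 |
| 0.3 × 0.4 | 0.12 | 0.71 |
| 0.3 × 0.5 | 0.15 | 0.91 |

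Weak confounding does not reach 0.15; moderate confounding does.

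**3. Raw weight at 6–12 weeks.** Assumptions, none in the article: growth 0.2 kg/week, visits uniform over the six weeks, SD at fixed age 0.55–0.65 kg. The window adds variance (0.2 × 6)²/12 = 0.12 kg².

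- SD 0.55: 0.15 × 0.55/√(0.3025 + 0.12) = 0.15 × 0.55/0.65 = 0.127; power 0.77.
- SD 0.65: 0.15 × 0.65/√(0.4225 + 0.12) = 0.15 × 0.65/0.737 = 0.132; power 0.81.

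**4. Total weight gain and birth weight.** Assumptions, none in the article: birth weight SD 0.55 kg and slope 0.17 kg per week of gestation; gestation SD s = 1.5–2.0 weeks; net maternal gain SD 5–7 kg with slope b = 0–0.4 kg/week. With no effect of maternal gain on birth weight,

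r = (0.55² + 0.17·b·s²) / (0.55 × √(SDnet² + 0.55² + 2 × 0.17·b·s²)).

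- SDnet 7, b = 0: 0.55/7.02 = 0.078.
- SDnet 5, b = 0: 0.55/5.03 = 0.109.
- SDnet 7, b = 0.4, s = 2: 0.5745/(0.55 × 7.06) = 0.148.
- SDnet 5, b = 0.1, s = 2: 0.3705/(0.55 × 5.04) = 0.134.
- SDnet 5, b = 0.4, s = 2: 0.5745/(0.55 × 5.08) = 0.205.

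The range is about 0.08–0.20. It passes 0.15 only when net gain varies little and also rises appreciably with gestation.

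**5. Cost of adjusting.** A partial correlation with k covariates replaces n − 3 by n − 3 − k. For a partial correlation of 0.15, power is 0.910 with one covariate, 0.908 with four, 0.907 with six and 0.905 with ten.

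**The case against.** The strongest reply is that the article condenses a longer protocol. It never says that the correlations are unadjusted, it does not exclude partial correlations, and a covariate list could sit in the full protocol or SAP. That is fair as far as a missing list goes. But the article does state the estimate, the type of coefficient, the target value and the power, all for an ordinary correlation, and it places regression elsewhere. The point concerns that stated choice.

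Other replies stand and limit the point:

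- BMI percentile and z-score are already age/sex adjusted, so a reader who inferred that sex is ignored throughout the primary outcomes would be wrong.
- A reader might infer that artefact will produce correlations at a threshold the study uses to declare findings. The article does not support this: 0.15 is a planning effect size, and the inputs in steps 2–4 are not in the article.
- The article does not say whether weight gain is total, net or per week. Step 4 applies only to total gain.
- Alpha 0.01 is tied to four exposure groups: glycemia, lipids, inflammatory markers and kidney function. Weight gain is not among them, so the significance probabilities in step 2 should not be carried over to it.
- Subgroup analyses by race and ethnicity are planned. They would give within-group estimates, though not as the primary analysis.
- The objective speaks of associations, which a raw correlation does estimate. Gestational age may also lie on the causal path, so adjusting for it changes the question being answered.

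**Conclusion.** The point holds in a limited form. As stated, the primary analysis cannot distinguish the three maternal exposures in its own objective. This follows from the design and needs no outside figure.

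For birth weight, infant weight and length, no age or sex adjustment is stated. For raw weight at 6–12 weeks this would cost about 10 to 14 points of power (0.91 to 0.77–0.81), given the assumed growth rate, SD and even use of the window. The figure does not extend to the later visits, which are given as single ages, or to BMI percentile and z-score.

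The built-in correlation between total weight gain and birth weight is about 0.08–0.20 under the stated assumptions. It could reach 0.15; the documents do not show that it will. The sample size is not in question: the same 675 analysed pairs support an adjusted primary analysis.

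**What to change.** - Make the primary estimate a partial correlation or standardised regression coefficient. Adjust for infant sex (where the outcome is not already sex-adjusted), race/ethnicity and maternal age, and for pre-pregnancy BMI when the exposure is weight gain or glycemia.
- Analyse infant weight and length as age/sex z-scores at exact age.
- Define gestational weight gain. When birth weight is the outcome, use gain net of birth weight or per week of gestation.
- State that r = 0.15 refers to the adjusted scale.
- Report estimates with and without gestational age, and keep the raw correlation as descriptive.

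The cost is a change of analysis wording, slightly more analysis work and two estimates to interpret. Table 2 already lists the covariates, no additional participants are needed, and power is essentially unchanged (0.907 with six covariates against 0.910).

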### **Analysis of the** primary outcomes

As described above, to examine associations among maternal risk measures, and offspring weight and body size, scatterplots and grouped box plots will be constructed to examine assumptions of linearity, symmetry, and homoscedasticity. To model changes in childhood BMI over time, we will use mixed effects models to fit a piecewise growth curve model which predicts childhood BMI as a function of time.

### Sub-group analyses

Because virtually all participants (or their offspring) will be of at least part AI or Hispanic heritage, we plan to analyze subgroups defined by race and ethnicity.

### Statistical methods in handling missing data

Information pertinent to reason for missing data will be collected. Analyses will be conducted to determine whether dropout rates are associated with any key covariates. Most standard analysis methods proceed under the assumption that missing data occur at random. The analyses of factors associated with dropout rates will be used to judge the extent to which this assumption is reasonable. Multiple imputation will also be used to handle missing data. If necessary, sensitivity analyses will be conducted to determine robustness of missing data assumptions.

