## Discussion

ETCHED is a life course study that will examine biological and environmental risk factors for obesity and cardiometabolic risk from the intrauterine period to early childhood and adolescence. The study population comprising Hispanic and American Indian/Alaska Native maternal/child dyads, were selected since they are at high-risk of obesity and type 2 diabetes compared to other racial/ethnic groups in the United States and planning and development of the protocol incorporated input from individuals in the target population. The steady funding support from the National Institutes of Health’s Intramural Research Program will ensure consistency and uniformity in implementing study procedures and data collection during the planned study duration of 23-years in this ongoing study. Given that obesity is a multifactorial complex disease, mechanistic insight is needed to predict which individual more precisely may be at risk for obesity and cardiometabolic disease and identify targets for intervention. To address this knowledge gap and improve understanding of early life obesity and associated metabolic risk, we will also conduct a unique phenotypic multi-omics based analytical approach utilizing clinical data, metabolomics, proteomics, and microbiomics, to investigate alterations at a molecular level and build a novel prediction model of those factors that may ultimately lead to obesity. Limitations include potential for loss to follow up and attrition over time, particularly in a vulnerable inner-city population. The large amount of data and biological samples collected longitudinally will provide a unique opportunity for a robust epidemiological assessment and additional integrated omics-based data analysis.

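### The plan judges missing at random by whether dropout is associated with observed covariates, a check that can reject only missing completely at random; sensitivity analysis is left optional with no other stated criterion

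*Protocol article*

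**What the plan says.** All the relevant text is in the protocol article, mainly under Statistical methods in handling missing data. In order, that section says:

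- Reasons are recorded: "Information pertinent to reason for missing data will be collected".
- Dropout is examined against covariates: "Analyses will be conducted to determine whether dropout rates are associated with any key covariates".
- The assumption is named: "Most standard analysis methods proceed under the assumption that missing data occur at random".
- The second item is used to assess the third: "The analyses of factors associated with dropout rates will be used to judge the extent to which this assumption is reasonable".
- Imputation is planned: "Multiple imputation will also be used to handle missing data".
- Sensitivity analysis is conditional: "If necessary, sensitivity analyses will be conducted to determine robustness of missing data assumptions".

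The section states no use for the recorded reasons and no criterion for when a sensitivity analysis becomes necessary. The sample-size section provides for 10% loss ("calculated with adjustment assuming 10% attrition"), and the Discussion lists loss as a weakness: "Limitations include potential for loss to follow up and attrition over time, particularly in a vulnerable inner-city population".

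**The concern.** Missing at random means that, given what was observed, dropout does not depend on the value that went unseen. It allows dropout to vary with maternal BMI, glycemia, income or earlier child size. A dropout table that shows such associations is evidence against missing completely at random (MCAR) and leaves MAR untouched. A table that shows none does not support MAR either, because MAR fails through the unseen measurement, on which the table is silent.

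Used as written, the check can mislead in both directions. It may raise doubt where imputation under MAR would be sound, or give reassurance where dropout depends on unseen child size in a way that distorts the association. The effect the study calls meaningful is small (r = 0.15), and the primary outcomes run over repeated visits to 24 months. A false reassurance could therefore matter to the primary results.

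**Working it through.** **1. The plan's own figure.** Inputs from the sample-size section and Table 3: 750 pairs recruited, 675 after 10% attrition, r = 0.15, alpha 0.01 (taken as two-sided).

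Power = Φ(atanh(r)·√(n−3) − z₁₋α/₂) = Φ(0.1511 × √672 − 2.576) = Φ(1.342) = 0.910.

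Table 3 states 0.92. The difference is about one point and has no bearing here. The calculation treats attrition only as a loss of numbers; r is assumed unchanged among those who stay.

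**2. The logic, case by case.**

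| Dropout table shows | MCAR | MAR |
|---|---|---|
| Association with observed covariates | Contradicted | Still possible |
| No association | Not contradicted | Neither supported nor contradicted |

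No result in the table separates MAR from missing not at random (MNAR). This step needs no simulation.

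**3. Association present, MAR true.** Simulated with 750 pairs, true r = 0.15, 2,000 replicates, dropout log-odds 1.0·X. A 5% test of X against dropout flags 100% of replicates at 10% loss. The MAR-based estimate is 0.150, which is unbiased. The complete-pair estimate is 0.145.

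**4. Association weak, MAR false.** Assumed dropout log-odds 0.3Y + 0.3XY, true r = 0.15, large simulated samples (2,000,000 records or more; runs agree to within about 0.002). The imputation column uses X and an earlier size measure assumed to correlate 0.7 with Y.

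| Loss | Correlation of dropout with X | Complete-pair r | r after imputation |
|---|---|---|---|
| 10% (protocol) | 0.035 | 0.117 | 0.134 |
| 20% (assumed) | 0.036 | 0.088 | 0.119 |
| 30% (assumed) | 0.033 | 0.062 | 0.106 |

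With 750 pairs and a true correlation of 0.035, a 5% test of X against dropout flags with probability about Φ(0.035 × √747 − 1.96) = Φ(−1.00) = 0.16.

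If complete pairs were analysed, power at 10% loss would be Φ(0.1175 × √672 − 2.576) = Φ(0.47) = 0.68, against 0.91 in step 1.

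**5. Dropout on child size alone.** With log-odds 0.3Y or 0.6Y, the complete-pair r stays between about 0.145 and 0.150 at 10% to 30% loss. The bias in step 4 comes almost entirely from the assumed XY term.

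**The case against.** Several points on the other side stand.

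- **The link to sensitivity analysis is inferred.** A reader might conclude that the plan makes sensitivity analysis depend formally on the dropout check, so that a clean table would switch it off. The text does not say so. The conditional sentence comes after the imputation sentence and has no stated trigger. Reasons for missingness, which bear on whether MAR is plausible, are also collected. It is fair to say only that the check is the sole judgement described.
- **The check is not useless.** It can reject MCAR, which matters for complete-pair correlations, and it shows which variables imputation needs. The section does not say that an association would be read as failure of MAR. If its wording meant MCAR, the check could refute that but not confirm it, and standard multiple imputation would still rest on an unexamined MAR assumption.
- **The covariate list may be wider than the exposure.** If an earlier child size correlated 0.7 with the outcome counts as a key covariate, the check in step 4 detects an association with power of about 0.45, 0.63 and 0.73 at 10%, 20% and 30% loss. The result still could not say whether MAR holds.
- **The bias figures depend on a chosen mechanism.** A reader might infer that any dropout related to child size would distort the primary correlation. Step 5 shows otherwise. Imputation with a good earlier measure also roughly halves the step 4 bias.
- **Detail belongs in the analysis plan.** The primary estimator, the list of auxiliary variables and the form of any delta adjustment are commonly settled there. Their absence from an article is not a fault.

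None of this rescues the sentence itself. It states a rule, and the rule does not test what it is said to test.

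**Conclusion.** The point holds in a limited form. The stated rule uses covariate associations to judge MAR, and those associations bear only on MCAR. This follows from the definitions and needs no assumption about this cohort. Sensitivity analysis is optional, and no criterion is given apart from what can be read into that check.

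The size of the consequence is not known from the documents. At the protocol's 10% attrition, under the assumed exposure-by-size mechanism, r falls from 0.15 to about 0.117 in complete pairs, or to about 0.134 with informative imputation. These figures illustrate what could happen and are not a forecast. The documents do not support reading them as expected bias, or reading the plan as having ruled out sensitivity analysis. The matter should be corrected, but it does not undermine the design.

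**What to change.** Reword the missing-data section in three places:

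1. State that the analysis of factors associated with dropout will be used to describe departures from MCAR and to choose imputation and auxiliary variables. Remove the statement that it judges MAR.
2. Delete the two-word condition that opens the sensitivity-analysis sentence.
3. Commit to one MNAR sensitivity analysis for the 24-month outcome, for example delta-adjusted multiple imputation, whatever the dropout analysis shows.

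The range of deltas and the auxiliary-variable list can be left to the analysis plan. The recorded reasons for missingness could inform that range. The cost is a few sentences and one extra analysis, with no new data and no change to visits or sample size.
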